# Preventing depression in the community by voluntary sector providers (PERSUADE): intervention development and protocol for a parallel randomised controlled feasibility trial

**DOI:** 10.1136/bmjopen-2018-023791

**Published:** 2019-10-03

**Keywords:** sub-threshold, depression, prevention, protocol, feasibility

## Abstract

**Introduction:**

Depression is now the most common illness worldwide affecting more than 300 million people. Studies modelling the impact of depression interventions have shown that the burden of depression cannot be minimised by more than 35% with existing treatments. There is a need to develop better preventative interventions. The overall aim of this programme of work is to develop interventions to reduce depression symptom scores and prevent development of depression in people with subthreshold depression. The objectives are to adapt a low intensity community-based depression prevention intervention, establish the acceptability and uptake of this model and conduct a parallel randomised controlled feasibility trial to inform a full-scale trial.

**Methods and analysis:**

Focus groups will be run with members of the public, voluntary sector providers and researchers to inform the adaptation of an existing depression prevention course. Sixty-four people with subthreshold depression, as represented by a score of between 5 and 9 on the Patient Health Questionnaire-9 depression measure, will be recruited to take part in the feasibility trial. Participants will be randomised equally to the intervention or usual care control groups. Participants in the intervention group will receive the new revised manual and attend a 1-day workshop delivered by voluntary sector service providers. Outcome measures will be completed 3 months after baseline. Quantitative data on recruitment, randomisation, attendance, retention, questionnaire completion rates will be collected. Primary analyses will be descriptive and a process evaluation will be conducted to assess the processes involved in implementing the intervention. Interviews will be conducted to explore acceptability and framework analysis will be used to analyse the data.

**Ethics and dissemination:**

The study has been reviewed and approved by NHS Research and Ethics Committee: NW-Greater Manchester East. The results will be actively disseminated through peer-reviewed journals, conference presentations, social media, the internet and community engagement activities.

**Trial registration number:**

ISRCTN23278208;Pre-results.

Strengths and limitations of this studyAdapting the intervention to a workbook and 1-day workshop will reduce costs, make it more accessible (lower burden) to participants and move the intervention from primary care to voluntary sector organisations.Recruiting people with subthreshold depression can be challenging and so the study will evaluate a number of different recruitment strategies and assess them to see how much time each takes and the associated yield.We are engaging substantively with members of the public as well as with voluntary sector services and charities to ensure the intervention is both feasible and acceptable.This is a feasibility trial and is not powered to show effectiveness of the intervention.

## Introduction

Depression has high prevalence and incidence,^1^ affects quality of life,^2^ productivity, fulfilment of social roles and increases mortality,^3 4^ leading to high service use and economic costs.^5^ Depression is a major contributor to global disease burden, predicted to become the leading contributor in high-income countries by 2030.^6^ Recent reports by the WHO show that depression is the leading cause of disability worldwide, affecting more than 300 million people.^7^ In a recent community cohort study of whites and British Pakistanis, prevalence of depression was 12.6%. At 6 months follow-up, 60.5% cases were persistently depressed and incidence of new cases was 17%.^8^

Modelling studies have shown that existing treatments cannot reduce the burden of depression by more than 35% even under ideal circumstances.^9^ Major depression can be prevented with current knowledge.^10 11^ Prevention may offer an opportunity to reduce the disease burden of depression further.^12^ A number of studies have examined the capability of prevention programmes to successfully reduce the incidence of depression.^13 14^ This is important from a public health perspective as duration of the disorder is inversely related to outcome, so that by the time cases are recognised, they are harder to treat. Developing an intervention aimed at both prevention and early treatment could potentially reduce the overall burden of depression.^6^

NICE guidelines (CG 90 and 91) advocate case finding by general practitioner (GP) for depression in high risk groups with physical comorbidities and those with history of depression. They recommend offering antidepressants or psychological interventions to people with moderate to severe depression.^15^ In the UK, access to psychological therapies for depression is delivered by Improved Access to Psychological Therapies (IAPT) teams. According to the service guidelines, they offer screening and then access to services for people scoring above 10 on the Patient Health Questionnaire (PHQ-9) screening tool.^16^ A range of evidence-based psychological interventions are delivered according to a stepped-care model for those with mild–moderate and moderate–severe depression.^17^

Less attention has been paid to subthreshold depression, defined as those who respond positively to case-finding questions on the PHQ-9 but do not have sufficient symptom scores on diagnostic criteria to screen positive for major depressive episode.^18^ Subthreshold depression is a major risk factor for progression and development of more severe depression^19 20^ and has been shown to have similar consequences.^21–23^

Previous UK trials have generally included cases with above threshold depression and have not looked exclusively at people with subthreshold depression. We could identify only 2 UK randomised controlled trials (RCTs) in the 2 published meta-analyses of 25 depression prevention trials.^13 24^ Both UK trials were aimed exclusively at pregnant women and published in 2000. An update of this meta-analysis included 34 RCTs with no further RCTs from the UK.^25^

An intervention for subthreshold depression needs to reduce the incidence of new onset depression but also improve outcome for those who do develop depression by reducing the length of the episode. GPs coordinating with voluntary sector organisations to deliver the intervention will potentially increase access for hard-to-reach groups.^26–28^ Depression treatment studies using lay health workers to deliver cognitive behavioural interventions have already been found effective in settings with few professional mental health providers.^29–31^ However, voluntary sector workers will need to be adequately trained and supervised in delivering a patient-centred intervention according to a treatment manual. Substance abuse treatment counsellors have successfully administered a version of the depression prevention intervention to treat depression in individuals in substance abuse treatment.^32^

We need to understand user and provider views about prevention strategies in subthreshold depression and their applicability to the UK health systems. There is uncertainty around the content, format, duration and use of voluntary sector workers to deliver such an intervention. We will aim to address these issues through involving users, providers, primary care staff and experts in this field and incorporating their opinions into the intervention and trial design.

The model we propose to use will be a psycho-educational intervention for prevention of depression in the form of a community-based workshop to be delivered to people with subthreshold depression. The proposed intervention will be adapted from the ‘Depression Prevention Course’ and include evidence-based cognitive-behavioural therapy (CBT) techniques, previously developed by Muñoz for preventing depression. The intervention is fully described in the book *The Prevention of Depression: Research and Practice*
33 and an online version of the manual is freely available.^34^ Many trials have already used versions of the manuals from the depression prevention course and have shown efficacy in diverse populations.^35–37^ The adapted intervention will be delivered via an accessible community workshop format as developed for depressed people by Brown and colleagues (self-confidence workshops).^27 28 38^

### Research objectives

The eventual aim of our research programme is to reduce depression symptom scores and prevent development of depression in people with subthreshold depression defined as PHQ score 5–9.^16^ This feasibility trial will follow the Medical Research Council (MRC) framework^39^ for the development and evaluation of complex interventions and has the following objectives:To adapt a low intensity community-based depression prevention intervention based on CBT model for adults with subthreshold depression deliverable by voluntary sector organisations.To establish the acceptability and uptake of this model by adults with subthreshold depression.To test the feasibility of conducting a successful trial of community-based depression prevention intervention for adults with subthreshold depression.

## Methods and analysis

### Patient and public involvement

Over a number of years, we have conducted research in collaboration with community-based voluntary organisations (Roby Church, Mind, Pakistani Resource Centre, Scaitcliffe Community Centre) in the North West. During past stakeholder events, it had been discussed that interventions should be made available which prevent depression in vulnerable people.

During the preparation of the funding application, we worked with voluntary sector organisations and providers (YARAN Community Services, Self Help Services, Manchester) to inform the proposed intervention content, delivery and research design. We also made presentations to a lay public group and incorporated their suggestions into the proposal. YARAN Community Services and Self Help Services, Manchester will continue to offer advice throughout the project. Phase 1 of the study involves community focus groups and at the end of the study community events will be used to feed back the results and to develop the proposal for a full trial for effectiveness and cost-effectiveness. Members of the public will be involved in the recruitment to the study by providing feedback on recruitment materials during the focus groups but will not be involved in the conduct of the study.

Qualitative interviews with participants in the intervention group will focus on their experiences of a, taking part in a study and b, all aspects of the intervention (manual and workshop) to explore acceptability, burden of the intervention and to further modify or adapt the intervention and trial design for a full trial.

### Phase 1: intervention development

#### Intervention and manual development

The ‘Depression Prevention Course’ developed by Muñoz^33 34^ will be adapted for this study. Box 1 above  shows key components of the original Depression Prevention Course.Box 1Depression Prevention CourseOriginally based on Social Learning TheoryThe intervention was developed using materials from the book ‘Control your Depression’ 1978Combines three methods used to treat depression:Increasing pleasant activities.Social skills training.Cognitive approaches.Delivered by trained CBT therapist8 group sessions delivered over 8 weeks51 page ‘Outlines for Participants’ manual (text only)

#### Focus groups

To tailor the intervention, focus groups will be held with users and providers.

A series of focus groups (3–5) will be run with a variety of groups including the general population, voluntary service providers from Self Help Services, Manchester and academic participants. The aim of the groups will be to get feedback on intervention content, delivery options, manual design, as well as recruitment methods. This will assist in the intervention adaptation and delivery and also in refining the recruitment methods and materials. As the different aspects are discussed, the groups will be asked to try to reach a consensus on their feedback, for example when offered a range of images, which do they think are the most engaging or in the case of terminology do they prefer ‘depression’, ‘low mood’ or ‘feeling down’ among other suggestions. The groups will be held at a location convenient to participants and last around 2 hours. Sessions will be audio-recorded, with consent, and transcribed.

#### Prevent depression intervention

Once we have run the focus groups and discussed the outcomes within the trial team, the original Muñoz manual will be redesigned as an accessible and easy-to-understand manual-based intervention. To support the manual and guide people in its use, participants will attend a 1-day (or two half-day) workshop. The aim is that offering a one-off psycho-educational group will improve access for a larger group of people. Asking participants to commit to 8 weeks of intervention when they do not yet have a diagnosable condition requires substantial resources and time commitment from service providers and participants. This workshop approach has been effective in a number of studies.^26 27^

### Phase 2: Feasibility trial

PERSUADE Protocol v2 (20/08/2017)

#### Design

A mixed method of feasibility trial and process evaluation to explore feasibility and acceptability of a depression prevention intervention.

#### Setting

Primary care and community, Greater Manchester UK.

Feasibility parameters: Best recruitment methods to identify people with subthreshold depression, participants willingness to be randomised, retention rates and outcome measure completion rates, acceptability of the intervention to both participants and facilitators, training of facilitators from voluntary sector services to deliver the intervention.

#### Inclusion criteria

Patients from primary care and the general community who are aged above 18 years and who score between 5 and 9 on the PHQ-9.^16^

#### Exclusion criteria

Candidates will be asked if they have any diagnoses for:Depression (score higher than nine on PHQ-9, or formal diagnosis of depression).Psychosis (self-report).Drug or alcohol use as primary diagnosis (self-report).Suicidal ideations (self-report).Non-English language speakers.

#### Participant recruitment

As this is a feasibility trial, a formal sample size calculation was not undertaken. The aim is to recruit a total of 64 patients to be randomised with equal probability to the intervention or usual care (ie, 32 to each). This is broadly in line with current guidance on feasibility trials^40^ and was considered sufficient to allow the formation of multiple groups for testing of the intervention and to provide sufficiently robust estimates of recruitment timelines and rates of loss to follow-up, within the limits of the available funding.

Considering the challenge of recruiting persons with subthreshold depression, a number of different recruitment strategies will be tried and assessed to see how much time each takes and the associated yield.

##### Recruitment through GP practices

GPs to refer patients recently screened with the PHQ-9 who scored between 5 and 9. They will either give out the study information during the consultation or post the patient materials to them.Searches will be carried out on GP practice databases to see if it is feasible to identify patients who have concerns about their mood but who have not been referred on to Improving Access to Psychological Therapies (IAPT) services due to scores below 9 on the PHQ-9. Searches will be done by practice staff or CRN support staff to identify potential participants and mail out the study information.Research staff to offer study information and to screen patients with PHQ-9 in GP waiting rooms if they are interested in taking part.

Network support will be sought from Greater Manchester NIHR Clinical Research Network (CRN) to ensure that the research project is conducted within the proposed time frame and recruitment targets are achieved. CRN will help with engaging primary care and liaising with GP at site.

##### Recruitment through advertising

Voluntary sector organisations (Scaitcliffe Centre, YARAAN Community, Self Help Services, Manchester) to direct self-referring patients by providing information about the study.Advertise in GP practice, library, community centres, citizens’ advice bureau, Sure Start and places of worship.Advertise on dedicated website, Facebook and Twitter.Advertise the study in local newspapers/radio and on Eventbrite.

##### Recruitment through other trials

Invite participants who are screened out from any ongoing depression trials run under Clinical Research Network. For those trials that agree, once patients have been screened as ineligible from other depression trials due to a low score on PHQ-9, they will send the details of PERSUADE trial to ineligible patients.

## Consent

Patients consenting to be contacted by the research team will be contacted over the phone or, if needed, visited at home or a convenient location. They will be given a participant information sheet (PIS) and have the study clearly explained to them, and they will also be given the opportunity to ask questions. The researcher will screen the participant for eligibility (as above) and if patients agree and meet the inclusion criteria they will be asked to sign and return the ‘participant consent form’ to enter the trial. Baseline assessments will then be self-completed or, if assistance is needed, by telephone.

### Confidentiality and data storage

All participants will be assigned a unique identification number which will be used for randomisation, data collection documents and analysis. Consent forms will be stored separately from participant data in locked filing cabinets. Publication of results will retain identification numbers to preserve anonymity, particularly where direct quotes are used. Only the primary research team will have access to the final trial data set.

### Ineligible and non-recruited participants

In cases where either moderate to severe depression (scoring 10 or more on PHQ-9) or thoughts of current self-harm or suicide are expressed, potential participants will be referred back to their GP. The PHQ-9 includes the statement: ‘Thoughts that you would be better off dead or of hurting yourself in some way’. If candidates score highly on this question (2 or 3), they will be advised to see their GP as soon as possible to discuss their mood.

### Randomisation

Participants will be randomised with equal probability to the CBT-based workshops or usual care (ie, 32 to each). Computer-generated block randomisation will be used. The allocation sequence will be set up by someone independent of the research team. Once a participant is randomised, the trial research associate will be informed by email, who will then contact participants. Participants will be informed of the allocation by letter or telephone. As this is an active intervention, they will not be blinded. Also as this is a feasibility trial and not a trial of efficacy, the research associate/PhD student will not be blind to allocation.

Figure 1 describes the process for the entry of participants into the trial and data collection points.

**Figure 1 F1:**
[figure not shown]
Recruitment and inclusion diagram.

We will follow the predetermined Stop–Go criteria for definitive RCTs:GO if 52 or more patients are recruited into the study (the target 64 minus 10%) .STOP if<39 (60%) patients recruited into study. STOP intervention is unacceptable to participants.

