### Outcomes

The primary outcome for this feasibility trial will be recruitment rates. Screening questions, demographical information, baseline and follow-up assessments will be recorded for each participant. Data will also be recorded regarding intervention attendance and retention rates for the 3-month follow-up.

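### The GO threshold of 52 recruits does not equal the 64 minus 10% from which it is said to be derived

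*Protocol article*

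**What the plan says.** The target is given in the section on participant recruitment: "The aim is to recruit a total of 64 patients to be randomised with equal probability". The Randomisation section repeats it as 32 per arm ("Participants will be randomised with equal probability to the CBT-based workshops or usual care (ie, 32 to each").

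The progression rule stands below Figure 1 and is introduced as fixed in advance: "We will follow the predetermined Stop–Go criteria for definitive RCTs". It has three parts:

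- GO: "GO if 52 or more patients are recruited into the study (the target 64 minus 10" per cent). A count is given, with its derivation in brackets.
- STOP on recruitment: "STOP if<39 (60%) patients recruited into study".
- STOP on acceptability: "STOP intervention is unacceptable to participants". No number is attached.

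The Outcomes section says "The primary outcome for this feasibility trial will be recruitment rates", so the two recruitment thresholds act on the trial's main measure.

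**The concern.** The GO criterion gives a number and the calculation behind it, and the calculation does not produce the number. A reader cannot tell from the article whether the count or the percentage was intended.

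The trial has no formal sample size calculation, and its primary analyses are descriptive. No hypothesis test decides whether a definitive trial follows. The recruitment thresholds are the only numerical part of that decision, and their value lies in being settled beforehand. If the total falls where the count and the percentage disagree, someone has to choose between them after seeing it, and pre-specification is lost at that point.

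**Working it through.** **Inputs.** Target 64 (Participant recruitment; Randomisation). GO at 52 or more, described as 64 minus 10%; STOP below 39, described as 60% (both below Figure 1).

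**Step 1: reproduce the GO figure as described.** 64 × (1 − 0.10) = 64 × 0.90 = 57.6. Counts are whole, so at least 57.6 means 58 or more. The printed figure is 52. The difference is 58 − 52 = 6 patients, and rounding 57.6 down to 57 still leaves a difference of 5.

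**Step 2: try other readings of the bracket.**

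- 64 / 1.10 = 58.2: not 52.
- 64 − 10 patients = 54: not a percentage, and not 52.
- 64 × 0.90 × 0.90 = 51.84, rounded up to 52: this fits, but needs the 10% to be taken twice, which the text does not say.
- 64 × 0.80 = 51.2, rounded up to 52: this fits, but is minus 20%.

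No single 10% reduction gives 52.

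**Step 3: what 52 is as a share of the target.** 52 / 64 = 81.25%, a reduction of 18.75%.

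**Step 4: reproduce the STOP figure.** 64 × 0.60 = 38.4, rounded up to 39. This agrees with the text. The same convention applied to 80% gives 52.

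**Step 5: classify every possible total up to the target.**

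| Total recruited | Share of 64 | GO by the count (52) | GO by the percentage (58) | Recruitment STOP |
|---|---|---|---|---|
| 0 to 38 | up to 59.4% | no | no | yes |
| 39 to 51 | 60.9% to 79.7% | no | no | no |
| 52 to 57 | 81.3% to 89.1% | yes | no | no |
| 58 to 64 | 90.6% to 100% | yes | yes | no |

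The count and the percentage disagree for six totals, 52 to 57. No total meets both GO and the recruitment STOP. Under the printed count, 13 totals (39 to 51) meet neither; with GO at 58, 19 totals (39 to 57) would meet neither.

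**The case against.** The best reply is that the operative text is an explicit count and the percentage is only a gloss. A team applying the rule as printed would use 52, and that number fits its neighbour, since 80% and 60% of 64, each rounded up, give 52 and 39. On this view the threshold is usable and only its label is wrong. That may well be what happened, but it is an inference. Nothing in the article says 80% or 20%, and the percentage is printed as plainly as the count. The contradiction stands until the sponsor says which is meant.

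A second reply concerns consequences. The discrepancy alters no participant's allocation, no measurement and no estimate, and recruitment and retention rates will be reported whatever the threshold. This is correct and limits the weight of the point to the progression decision.

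Several stronger readings are tempting, and the documents do not support them:

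- A reader might infer that the rule can return GO and STOP together on recruitment. It cannot. A total of 52 to 57 that misses the percentage is not thereby a STOP.
- A reader might infer that the absence of a rule for 39 to 51 is an error. Two thresholds with a band between them are not contradictory, and the band may be a deliberate zone for review. The article condenses a separate protocol (version 2) that is not shown and may define it. This is a question to the sponsor.
- A reader might add the 6 and the 13 totals and call 19 affected. They are different in kind: six have a contradictory criterion, and thirteen have no action stated in the article.
- A reader might suppose that the total is most likely to fall in these ranges. The article calls recruitment challenging but gives no forecast, so no probability can be attached.
- A reader might note that 52 and 39 are exactly 80% and 60% of 65 and infer a different target. No section gives 65, and rounding up from 64 explains both counts.

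**Conclusion.** The GO criterion is wrong as written: 52 is not 64 minus 10%. The stated derivation gives 58, and the printed count corresponds to 81.25% of the target. The effect is confined to totals of 52 to 57, where GO depends on which half of the criterion is read. It matters because this is the only numerical progression rule in the article and it acts on the primary outcome.

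This rests on the target of 64, which the article gives consistently, and on the ordinary meaning of a percentage reduction. That 10% is a slip for 20% is plausible from the STOP figure but not established. The range between STOP and GO is a secondary matter for clarification and not a demonstrated fault.

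**What to change.** State one GO threshold, with a percentage that reproduces it, before the recruitment total is known. There are two options:

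- GO if 52 or more are recruited (80% of 64 = 51.2, rounded up), or
- GO if 58 or more are recruited (64 minus 10% = 57.6, rounded up).

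STOP below 39 (60% of 64, rounded up) can stay as it is.

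As a clarification, say what applies between STOP and GO, with limits that match the chosen threshold: 39 to 51 if GO is 52, or 39 to 57 if GO is 58. If GO moved to 58 while the middle band stayed at 39 to 51, totals of 52 to 57 would be left without a decision. If the full protocol already defines this band, a reference to it is enough.

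The cost is a sentence or two of correction, with no change to design, sample size or data collection. Keeping 52 changes only the printed percentage. Choosing 58 makes GO harder to reach, by six patients.

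### The Stop–Go rule sets numbers for recruited head-count only: 3-month retention and outcome completion have no criterion, and the acceptability STOP has no cut-off

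*Protocol article*

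**What the plan says.** The progression rule stands in the Randomisation section of the protocol article, below Figure 1, and is presented as fixed in advance. It has three parts, one for GO and two for STOP:

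- GO: "GO if 52 or more patients are recruited into the study (the target 64 minus 10" (a percentage; the quote ends before the sign).
- STOP, first on recruitment and then on acceptability: "STOP if<39 (60%) patients recruited into study. STOP intervention is unacceptable to participants".

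The list of feasibility parameters under Setting is wider. Besides recruitment methods and facilitator training it includes "participants willingness to be randomised, retention rates and outcome measure completion rates, acceptability of the intervention to both participants and facilitators". Under Outcomes, "The primary outcome for this feasibility trial will be recruitment rates", and attendance and 3-month retention are also to be recorded. The Participant recruitment section defends the target of 64 partly on the ground that it gives adequate estimates of recruitment timelines and loss to follow-up. The Statistical analysis section says that outcome summaries and attrition will feed the sample size of the definitive trial.

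Evidence on acceptability is planned in several places: the CSQ-8 at 3 months (Quantitative outcomes), up to 15 participant interviews (Qualitative process evaluation), and records of engagement and of staying for the whole workshop (Format and content of the intervention). None of these sections says what result would count as unacceptable.

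**The concern.** A progression rule should respond to the quantities that the feasibility trial was set up to learn about. Here the numerical part responds to one of them. Retention and outcome completion decide whether a definitive trial with a 3-month PHQ-9 endpoint can be run, and they help to justify the size of this study, yet no value of either changes the decision.

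The acceptability STOP is the only other safeguard, and it is left to unstructured judgement. It concerns the intervention, so it does not naturally capture loss to follow-up, least of all in the usual care arm, where nobody receives the workshop. It is also weakest when attrition is high, because the CSQ-8 comes only from people who return the 3-month questionnaire.

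At stake is the trial's main product. A GO could be declared although the means, SDs and attrition rates carried into the next sample-size calculation come from a small and self-selected remainder.

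**Working it through.** **Inputs from the protocol article.** Target 64, 1:1 allocation, 32 per arm (Participant recruitment; Randomisation). GO at 52 or more, STOP below 39 (Randomisation, below Figure 1). No planned retention, attendance or recruitment duration is printed, so every such figure below is an assumption.

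**1. The plan's own thresholds.**

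- GO: 64 × 0.90 = 57.6, so 58 people. The stated 52 is not reproduced: 52/64 = 81.25%, which is 18.75% below target. It matches 64 × 0.80 = 51.2, rounded up to 52.
- STOP: 64 × 0.60 = 38.4, rounded up to 39. This is reproduced (39/64 = 60.9%).
- From 39 to 51 recruited, neither numerical condition applies and no decision is stated.

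The mislabelled percentage and the gap are separate defects. They matter here only because they mean that the rule needs redrafting anyway.

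**2. The rule as a function.** As written, GO holds when recruited ≥ 52 and the intervention is not judged unacceptable. Retention and outcome completion do not appear. Attendance appears only if someone chooses to read it as evidence on acceptability.

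**3. Varying retention at the GO threshold.** 52 recruited at 1:1 gives 52/2 = 26 per arm.

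| Assumed retention | Followed up (of 52) | Per arm, about | Wilson 95% CI | Numerical rule |
|---|---|---|---|---|
| 90% | 47 | 23–24 | 79–96% | GO |
| 50% | 26 | 13 | 37–63% | GO |
| 30% | 16 | 8 | 20–44% | GO |

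The decision is the same in each row, although the information available for planning falls by about two thirds (16/47 = 0.34).

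**4. Count against rate.** The primary outcome is a rate and the rule uses a count. With assumed durations of 6, 12 and 24 months, 52 recruits are 52/6 = 8.7, 52/12 = 4.3 and 52/24 = 2.2 per month. The printed rule treats all three alike, because it does not mention a recruitment period.

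**5. How firmly any new band could be applied.** Exact 95% intervals for results near 80%:

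- 42/52 (81%): 67.5% to 90.4%, half-width (90.4 − 67.5)/2 = 11.5 points.
- 26/32 (81%): 63.6% to 92.8%, half-width (92.8 − 63.6)/2 = 14.6 points.

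Both intervals straddle 80%. A threshold at that level can guide a decision but cannot act as a sharp test.

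**The case against.** The strongest reply has four parts.

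First, the rule is not purely a head-count. The acceptability STOP is a separate condition, and mass non-attendance at a one-off workshop could reasonably trigger it. This stands. A reader might infer that the trial must return GO even if most participants miss the workshop, but the article does not support that. It supports the narrower statement that nothing in the rule links attendance to the decision.

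Second, acceptability is not unmeasured. The CSQ-8, the interviews and the workshop records all bear on it, and a qualitative judgement is legitimate in a mixed-methods study. This also stands: what is missing is a cut-off or a stated basis, not data.

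Third, a reader might infer that recruitment is open-ended, so that 52 could be reached simply by waiting. The article does not support that either. The section on recruitment through GP practices refers to a planned time frame, and the target was set within the funding available. The period probably stands in the full protocol, which is not shown. What remains is small: the rule as printed does not refer to that period.

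Fourth, attrition is reported and used in planning, and the protocol expects little of it after a single-session intervention. It could therefore be left to descriptive judgement. This answers only in part. The article gives no figure for the expected loss, and it presents a complete rule fixed in advance. Once such a rule exists, a parameter outside it has no formal bearing on GO, even though the protocol lists that parameter among those to be tested.

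**Conclusion.** The point holds in this form. The Stop–Go rule has numerical criteria for recruited head-count only. Retention and outcome completion at 3 months, which are named feasibility parameters and part of the case for 64 participants, have no criterion. The acceptability STOP has no cut-off and no stated link to attendance or the CSQ-8. Heavy loss to follow-up is therefore compatible with GO.

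The size can only be illustrated: 52 × 0.50 = 26 people with 3-month data, about 13 per arm, and the rule is still met unless the intervention is separately judged unacceptable. The 50% is an assumption, not a forecast, and nothing in the article suggests that such loss is likely. The conclusion rests on the rule being complete as printed. If the full protocol holds further progression criteria, it lapses to that extent. Participants and the planned descriptive analyses are unaffected; the decision to proceed is what can go wrong. The change should be made, but the study does not fail without it.

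**What to change.** Before any outcome data are seen, amend the rule as follows:

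- Add a criterion for 3-month PHQ-9 completion, overall and shown by arm.
- Add a criterion for workshop attendance in the intervention arm.
- State that attendance and the intervention-arm CSQ-8, together with the interviews, inform the judgement of unacceptability, and who makes it.
- Tie the recruited count to the recruitment period already planned for the study.

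Bands such as proceed at 80% or more, proceed with changes from 60% to 79%, and stop below 60% would serve as an example. They do not come from the article. Given the intervals above, they should be reported with their 95% limits and used to guide the decision. In the same edit, correct the percentage attached to 52 and state what happens from 39 to 51 recruited.

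The cost is modest. Every quantity is already collected, so no new data or participant burden is needed. GO becomes somewhat harder to reach, and with about 26 to 32 people per arm chance alone may keep a workable design out of the top band. The Ethics and dissemination section shows recruitment channels already in use, so the change needs a dated amendment recording that it preceded sight of outcome data.
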